## Methods

2

### Study design

2.1

The REHAB + trial is a multicenter, prospective, matched controlled observational trial with participation from the following centers: Zuyderland Medical Center (Heerlen, The Netherlands), Hospital Virgen de la Victoria de Málaga (Malaga, Spain), and Hospital Universitari Vall d’Hebron (Barcelona, Spain). The medical ethical commission of all participating centers approved the study protocol. Inclusion started in November 2021 and the last patient was enrolled in Februari 2024. The trial is registered at clinicaltrials.gov with registration number NCT05207072.

### Study population

2.2

Patients eligible for CR who are unwilling to participate in either CTR or center-based CR are allocated to the non-participation category of the study. Patients eligible for the trial are (N)STEMI patients over 18 years old that meet the eligibility criteria to participate in a CR program. Eligibility criteria for CR include the physical ability to safely perform an exercise test. Patients with myocardial ischemia during the exercise test, and judged unsafe for CR participation by a trained cardiologist, are excluded from the trial. Patients are required to have the mental ability to cooperate by following instructions from their coaches and need the proper knowledge to comprehend the native language of the coaches. Patients participating in CR at a different CR center during or after hospitalization are excluded. The research nurse and cardiologist reserve the right to exclude patients deemed unfit for CR due to severe comorbidities. A complete overview of in- and exclusion criteria is found in Table 1.

**Table 1 T1:** In- and exclusion criteria for cardiac (tele) rehabilitation.

Inclusion criteria	
CR	Recent myocardial infarction [(N)STEMI only]
CR	Signed written informed consent
CTR only	Smartphone capable of installing REHAB + application
Exclusion criteria	
CR	Contra-indication for CR (such as risk for safety and limited lifespan)
CR	Mental impairment leading to an inability to cooperate
CR	Severe impaired ability to exercise (including an inability to safely perform the exercise test)
CR	Insufficient knowledge of the native language
CR	Current participation in CR (at CR center or elsewhere)
CR	Participation in a CR program elsewhere after index myocardial infarction

### Treatment allocation

2.3

The coaches and investigators are explicitly instructed to refrain from advising patients on their choice between CTR and center based CR to avoid bias. However, coaches and investigators are allowed to advise patients to participate one of either CR programs, as that is common practice. Providing neutral information about the advantages and disadvantages of both treatment options is allowed. After signing, all participants are free to choose between CTR and center-based CR. Non-participants are registered as such, provided they meet eligibility criteria and sign informed consent. The patients meet with the nurse after an exercise test to inform them of their allocation choice. The flowchart of the inclusion procedure is found in Figure 1.

**Figure 1 F1:**
[figure not shown]
Flowchart of the inclusion procedure.

### Cardiac rehabilitation

2.4

Cardiac rehabilitation nurses screen potential participants during hospitalization. Preferably, they make first contact during the hospitalization phase to motivate patients to participate in CR and inform them about the content of the program. Afterwards, the nurses contact patients by phone after discharge to arrange a first appointment. The aim is to start CR as soon as possible, usually within 3–4 weeks after discharge from the hospital after PCI and 6 weeks after CABG. All patients will start the CR program with an exercise test to ensure safe rehabilitation and to provide information on the exercise capability of the patient. The nurse provides patients with health modules from the library of content to tackle modifiable risk factors (e.g., nutrition, exercise, psychology, and the societal impact of cardiovascular disease). A specialized psychologist works with patients that experience anxiety after their myocardial infarction. A social worker discusses any problems experienced at home.

### Center-based cardiac rehabilitation

2.5

The exercise-training program of the center-based CR program lasts for approximately 6–8 weeks depending on the needs of the patients. The educational, psychological, and lifestyle parts of the CR program are usually completed within these 6–8 weeks. The completion of center-based CR is marked by the completion of the exercise-training program and by a wrap-up meeting with the nurse. The nurse will ask to evaluate the program, reflect on the newly learned health behavior and motivates patients to continue with healthy behavior change at home.

### Cardiac telerehabilitation

2.6

#### REHAB + application

2.6.1

The CTR program start with the installation of the REHAB + app and instructions on how to use the app (Livahealthcare.com). The REHAB + app provides participants and coaches with asynchronous, remote-access communication via text or video messaging (Figure 2). Coaches can share additional health information from the comprehensive library of content to aid health goal progression. Coaches can motivate or support participants depending on their goal progression. Participants can upload and monitor health status information [e.g., mode of physical activity, rate of perceive exertion (BORG-score), blood pressure, glucose levels, eating habits, sleeping habits and smoking habits]. The REHAB + app receives physical activity input from a wearable heart rate device and/or pedometer. Each participating center is free to make use of clinically approved wearables they see fit for supporting remote exercise training supervision. Participants are allowed to make use of a wearable heart rate device of their own if it matches with the requirements of the app. The time and effort the coaches provide each patient is mainly concentrated during the first few weeks of CR. Moreover, when patients show sufficient goal progression and self-efficacy, time and effort provided by the coaches will be toned-down. The CTR program will provide tele monitoring for 48 weeks, after which the CTR program ends and patients are motivated to continue their newly learned health behavior and goal progression at home.

**Figure 2 F2:**
[figure not shown]
Overview of cardiac telerehabilitation via the liva app.

#### Exercise

2.6.2

The physiotherapist creates a personalized exercise program that fits the exercise capability of the participant. We minimized the number of in-person training sessions (max 2), only explaining the essentials and guiding participants in the use of the REHAB + app. Each participating center is free to structure their own exercise-training program in adherence to European and national guidelines. Participants are encouraged to perform the exercises taught by their physiotherapist at home. Patients receive advice on other modes of exercise at home from the physiotherapist (e.g., walking or cycling, and the duration and intensity of the exercise). The REHAB + app allows participants and coaches to keep track of their perceived intensity during exercise (via BORG-scale). Participants can also keep track of the frequency in which they exercise in the 48 weeks they can use the REHAB + app.

### Data collection

2.7

Data are collected at program initiation (T0), three months after initiation (T1) and twelve months after initiation (T2). Data collection from non-participants only include baseline characteristics at T0. Researchers collect data from the electronic health record. Exercise-related data will be collected by Liva (Livahealthcare.com). Data will be made available after all participants completed their CTR program. Participants receive questionnaires by e-email or by postal mail. Participant data is pseudo anonymized. The SPIRIT diagram is found in Table 2.

**Table 2 T2:** SPIRIT diagram for REHAB+ study.

	Study period			
	Enrolment	Allocation	Post-allocation	Close-out
Timepoint^a^	*-t_1_*	0	*t_1_*	*t_2_*
Enrolment:				
Eligibility screen	(X)			
Informed consent	(X)	(X)		
Allocation		(X)		
Interventions:				
Center-based cardiac rehabilitation				
Cardiac telerehabilitation				
Non-participation				
Assessments:				
Baseline characteristics^b^		(X)		
Medication, blood pressure, BMI		(X)	X	X
Blood sampling^c^		X	X	X
Exercise test		X		X
Adherence and compliance			X	X
Adverse (cardiac) events			X	X
Fägerstrom test		X	X	X
SF-36 questionnaire		X	X	X
IPAQ-SF		X	X	X
eHIQ^d^			X	

Cells marked with (X) are data gathered for center-based CR, CTR and non-participants of CR. Cells marked with X are data gathered for both center-based CR and CTR. SF-36 36-Item Short Form Health Survey, IPAQ-SF International Physical Activity Questionnaire-Short Form, eHIQ e-Health Impact Questionnaire.

^a^
-t1= Period between hospitalization and start cardiac rehabilitation, t0 = start cardiac rehabilitation, t1 = three months, t2 = twelve months.

^b^
Demographics, medical history, risk factors, coronary angiography outcome, mode of revascularization, type of acute coronary syndrome, left ventricular ejection fraction and twelve lead electrocardiogram.

^c^
Lipid profile, kidney function and Hb1Ac.

^d^
Participants in the cardiac telerehabilitation group receive an extended questionnaire containing specific questions about the REHAB + app.

The main source of baseline data extraction is the electronic medical file, besides questionnaires. Baseline characteristics include age, sex, ethnicity, employment status, marital status, living situation and distance from the hospital. Traditional risk factors data collection include a medical history of hypertension, hypercholesterolemia and diabetes (including HbA1c), current smoking status and family history of cardiovascular disease. Moreover, a researcher from the research team extracts the medical reason for CR participation, medical history relevant to cardiovascular diseases and the current use of cardiovascular medication. Finally, information from focus tests, such as heart ultrasound (LV function), coronary angiography (with or without modes of revascularization) and electrocardiography will be interpreted and obtained by a medical doctor from the research team. Finally, results from the exercise test include blood pressure, peak blood pressure, METS score and ECG changes at peak exercise capacity.

The REHAB + app monitors adherence and compliance of CTR participants. Adherence is defined as the number of dropouts and the reason for drop-out in relation to participants completing CTR. Compliance is defined as the number of logins and the proportion of planned exercise sessions completed, as well as which sessions are completed (i.e., exercise, quitting smoking). Information from i.e., the heart rate monitor, goal progression, data input by the participant (e.g., BORG scale) and interaction with the coaches will be logged in the app.

#### Questionnaires

2.7.1

Participants evaluate quality of life at baseline, three months and twelve months using the 36-Item Short Form Health Survey (SF-36) version 2.0. Each participating center used a validated version translated to the local language (34, 35). The questionnaire provides a score on eight domains. These translate to a physical component score and a mental component score. Domains mostly related to the physical component score has the most pure interpretation for chronic medical conditions (36).

A coach and cardiologist assess physical fitness at baseline using an exercise test. The participant completes the exercise test by exerting their maximal workload. However, the test stops prematurely if the participant exhibits angina. Physical activity is evaluated for all participants using the International Physical Activity Questionnaire-Short Form (IPAQ-SF) (37, 38). The IPAQ-SF is a 7-item questionnaire, which allows the calculation of metabolic equivalents (METs score) using self-reported physical activity intensity and frequency.

The modifiable risk factors are documented during hospitalization, from which baseline data on the use of tobacco products is extracted. Patients fill out the Fagerström test, testing nicotine dependency at baseline, three months and twelve months. The Fagerström test is a validated (39, 40), 5-item questionnaire with a scoring system that categorizes dependency on nicotine in four categories (barely dependent, to lightly dependent, to moderately dependent, to strongly dependent).

CTR participants receive the e-Health Impact Questionnaire (eHIQ) at baseline, three months and twelve months, evaluating their previous general health experience (11-item questionnaire) and the digital health experience of the REHAB + app (15-item questionnaire). Center-based CR participants only receive the general health experience section. The eHIQ is validated for Dutch participants (41). An official translation agency translated the eHIQ into Spanish for the Spanish centers with permission of the original authors.

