**Methods:**

The REHAB + study is a multicenter, prospective, matched controlled, observational study that includes (N)STEMI patients eligible for cardiac rehabilitation. We aim to enroll 300 participants for cardiac telerehabilitation and 600 for center-based cardiac rehabilitation. Participants opting for cardiac telerehabilitation (REHAB+) will be matched with center-based cardiac rehabilitation participants. Additionally, characteristics of patients unwilling to participate in either center-based rehabilitation or telerehabilitation but are willing to share their demographics will be collected. The primary endpoint is quality of life measured with the SF-36 questionnaire at three and twelve months, with patient-related characteristics driving intervention choice as the most important secondary endpoint. Secondary endpoints include physical activity, modifiable risk factors, and digital health experience. The trial is registered at clinicaltrials.gov with registration number NCT05207072.

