### Sample size calculation

2.8

The sample size calculation is based on an expected increase in quality of life after one year, specifically the physical component score change of the SF-36 questionnaire V2.0. Previous research (42) found baseline quality of life physical component score of 48.4 + - 5.8 at program initiation and 53.3 + - 3.9 after 12 months. We estimated an increased score to 55 + - 7.0 for CTR patients. The sample size calculation, using the Hotelling Lawley Trace test, resulted in a sample size of n = 268 per group (power = 0.8 and alpha = 0.05). Assuming 10% withdrawal or incomplete data, we aim for n = 300 participants per group. We expect a 1:2 ratio of participants choosing CTR vs. center-based CR. We aim to continue inclusion until 300 participants are included in the CTR group, with enough participants to match in center-based CR (600). This will likely result in 300 participants per participating CR center (100 participants choosing CTR and 200 participants choosing center-based CR).

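### No Spanish validation of the eHIQ is stated, although two of three centers are Spanish and the stated test has no center or language term: report eHIQ by language and stratify the general-section comparison

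*Protocol article*

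**What the plan says.** The abstract lists the endpoint: "Secondary endpoints include physical activity, modifiable risk factors, and digital health experience". Section 2.7.1 (Questionnaires) describes the eHIQ as the instrument. It has an 11-item general section and a 15-item section on the app. CTR participants receive both, whereas "Center-based CR participants only receive the general health experience section".

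On language versions, section 2.7.1 treats two instruments differently. For the SF-36: "Each participating center used a validated version translated to the local language (34, 35". For the eHIQ: "The eHIQ is validated for Dutch participants (41", and then "An official translation agency translated the eHIQ into Spanish for the Spanish centers with permission of the original authors".

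Section 2.1 names one Dutch and two Spanish centers: "Zuyderland Medical Center (Heerlen, The Netherlands), Hospital Virgen de la Victoria de Málaga (Malaga, Spain), and Hospital Universitari Vall d’Hebron (Barcelona, Spain". Section 2.8 gives the expected split: "This will likely result in 300 participants per participating CR center (100 participants choosing CTR and 200 participants choosing center-based CR".

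Section 2.9 assigns two-group continuous data to an independent t-test, or a Mann-Whitney test if the data are not normal. It does not mention the eHIQ specifically and names no center, country or language term. Section 2.3 leaves the choice of program to the patient. Section 3.1 accepts that the expected ratio may not be met and that centers may differ locally.

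**The concern.** Agency translation and permission from the authors show that the Spanish text was properly obtained. They do not show that a given score means the same in both languages. The article reports validated local versions for the SF-36 and validation in Dutch for the eHIQ, but reports none for the version that most participants are expected to complete.

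Two results could be affected if the versions are not equivalent:

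- **App section (CTR only).** There is no comparison group in which a shift could cancel, so a description pooled over centers would carry it.
- **General section (both groups).** A shift enters the CTR versus center-based difference if the two groups contain different shares of Spanish respondents. Free choice of program allows this, and the stated test would not correct for it.

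**Working it through.** **Inputs.** Three centers, one Dutch and two Spanish (section 2.1). Expected per center: 300 participants, of whom 100 choose CTR and 200 center-based CR (section 2.8). The size of any translation shift is not in the documents. It is written *d*, an assumed constant added to every Spanish response relative to the Dutch version. The article gives no eHIQ scale or SD, so *d* is expressed in SD units.

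**Plan's own totals.** CTR: 3 × 100 = 300. Center-based: 3 × 200 = 600. Both agree with section 2.8.

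**Expected Spanish share, s.**
- CTR: 2 × 100 / 300 = 66.7%
- Center-based: 2 × 200 / 600 = 66.7%
- All: 2 × 300 / 900 = 66.7%

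**App section, pooled CTR mean.** Movement = s_CTR × d = 0.667 d.
- d = 0.1 SD gives 0.07 SD
- d = 0.3 SD gives 0.20 SD
- d = 0.5 SD gives 0.33 SD

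**General section, unstratified group difference.** Bias = (s_CTR − s_CB) × d. The planned totals are kept (300 per center, 300 CTR, 600 center-based), and uptake is varied as an assumption:

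| CTR uptake, Dutch / each Spanish center | Spanish share, CTR | Spanish share, center-based | Bias | At d = 0.3 SD |
|---|---|---|---|---|
| 33.3% / 33.3% (as planned) | 200/300 = 66.7% | 400/600 = 66.7% | 0 | 0 |
| 50% / 25% | 150/300 = 50% | 450/600 = 75% | −0.25 d | −0.075 SD |
| 25% / 37.5% | 225/300 = 75% | 375/600 = 62.5% | +0.125 d | +0.0375 SD |

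**Why stratifying works.** Within a language, both groups carry the same *d* (Spanish) or none (Dutch), so each within-language difference is free of it. So is any weighted average of those differences. This needs the shift to be additive and equal in the two groups. It does not require knowing whether the shift comes from translation or from the center.

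**Precision.** With a common SD:
- By-language CTR means: intervals are wider than the pooled one by √(300/100) = 1.73 for Dutch and √(300/200) = 1.22 for Spanish.
- Stratified group difference in the 50% / 25% example: Dutch variance factor 1/150 + 1/150 = 0.01333 (information 75); Spanish 1/150 + 1/450 = 0.00889 (information 112.5). Combined variance is 1/187.5 = 0.00533, against 1/300 + 1/600 = 0.00500 unstratified. The interval is √(0.00533/0.00500) = 1.03 times as wide.

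**The case against.** The other side has strong points.

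**Validation.** A reader might infer that the eHIQ is validated in Dutch alone and that the Spanish version is unvalidated. The text says neither. It reports Dutch validation and is silent on any Spanish check, a detail that a condensed article may omit. It openly discloses how the Spanish text was made. What stands is that no Spanish validation is stated, in a section that states validated local versions for the SF-36.

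**Pooling.** A reader might also infer that the plan pools all centers, so that the score is already a mixture of language and experience. Section 2.9 does not say this. It lists general tests, and reporting by country may be laid down in a fuller document that is not shown. What stands is that the test as stated has no center or language term.

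**Size.** No eHIQ scale, SD or evidence of a shift is given, so any shift in points would be uninterpretable. The app section has no between-group test, so the risk there is to a description. In the general section an additive shift cancels exactly under the planned split. It would also cancel if CTR participants were matched to center-based participants within center, or if change from baseline were compared. The article specifies neither. Uptake of 50% against 25% with an assumed 0.3 SD shift yields only 0.075 SD.

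**Separability.** Language coincides with country, so no analysis of these data can distinguish translation from real differences between the countries. The article plans no Dutch-Spanish comparison either. Both points are correct. They limit what may be concluded, but the stratified group contrast does not depend on that separation.

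**Conclusion.** The point holds in a limited form and is minor. No Spanish validation of the eHIQ is stated, about two thirds of participants are expected at Spanish centers, and the stated test does not take account of center or language. Non-equivalence is a possibility, not something the documents demonstrate.

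If it exists, a pooled CTR mean of the app section carries two thirds of the shift. The general-section comparison carries none under the planned equal uptake, and one quarter of the shift in the 50% against 25% example. These results rest on a constant additive shift, on the planning split (an expectation, not an observed share) and on assumed uptake rates. Because patients choose freely and section 3.1 allows for departures from the expected ratio and for local differences, equal uptake cannot be relied on.

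The primary endpoint uses the SF-36, for which validated local versions are stated, and the sample size is built on its physical component score. Neither is affected.

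**What to change.** 1. Report eHIQ scores, and the app section in particular, separately for Dutch and Spanish respondents.
2. For the general section, replace the unstratified t-test or Mann-Whitney test with a CTR versus center-based estimate stratified by language or center. Center strata lie within language, so they serve the same purpose.
3. Draw no conclusion from a Dutch-Spanish difference in eHIQ scores.
4. Report the Spanish version's reliability on the collected responses, or cite existing validation evidence if there is any. Label the reliability result as supplementary: internal consistency would look the same whether or not a uniform shift is present.

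No new data are needed, which matters because section 2.1 reports that enrolment has closed. The cost is wider intervals for the by-language results, most of all for the roughly 100 Dutch CTR participants, and a very small loss of precision in the stratified contrast (about 3% in the example worked above).

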### Sample size calculation

2.8

The sample size calculation is based on an expected increase in quality of life after one year, specifically the physical component score change of the SF-36 questionnaire V2.0. Previous research (42) found baseline quality of life physical component score of 48.4 + - 5.8 at program initiation and 53.3 + - 3.9 after 12 months. We estimated an increased score to 55 + - 7.0 for CTR patients. The sample size calculation, using the Hotelling Lawley Trace test, resulted in a sample size of n = 268 per group (power = 0.8 and alpha = 0.05). Assuming 10% withdrawal or incomplete data, we aim for n = 300 participants per group. We expect a 1:2 ratio of participants choosing CTR vs. center-based CR. We aim to continue inclusion until 300 participants are included in the CTR group, with enough participants to match in center-based CR (600). This will likely result in 300 participants per participating CR center (100 participants choosing CTR and 200 participants choosing center-based CR).

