Previous research (7) explored the factors leading to non-participation in a telerehabilitation trial. Results show that factors leading to non-participation in this telerehabilitation trial (7) are associated with a worse cardiovascular risk profile (e.g., high age, a higher prevalence of modifiable risk factors, lower exercise capacity), lower prevalence of high education, lower prevalence of employment, and shorter travelling distance to the nearest hospital. Our hypothesis matches these results i.e., that patients not interested in CTR have a worse cardiovascular risk profile, a lower social economic status, and live closer to the nearest hospital than patients who are interested. The REHAB + study is the first large (>150 patients) multicenter and multinational prospective observational study to evaluate the effect of cardiac telerehabilitation in daily practice. It provides the possibility to gain experience with implementing cardiac telerehabilitation. Our study design differs from previous research by its size, design (observational instead of RCT) and inclusion in different European centers and countries. It provides beneficial information about patient characteristics and results. The aim of the REHAB + trial is to identify which parameters influence the decision to participate in center-based CR, CTR, or decline participation in CR. We will compare quality of life, physical activity, and modifiable risk factors before, during and after program completion. We expect an improvement in quality of life, specifically the physical component, in both center-based CR and CTR.

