### Statistical analysis

2.9

Continuous data will be analysed with the independent T-Test (or Mann-Whitney U test for non-normal distribution of data). Categorical data will be analysed using the chi-squared test (two groups) or ANOVA (> two groups). The One-way ANOVA test (or Kruskal Wallis test for non-normal distribution of data) will be used to analyse >two continuous data categories. The impact of multiple variables on allocation is analyzed using the multinomial regression analysis. All statistical tests are considered significant at P < 0.05. Statistical analysis will be performed on the latest version of IBM SPSS Statistics or R.

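### Section 2.9 names no baseline-adjusted or repeated-measures analysis for the SF-36 physical component score, which forgoes precision, and it leaves open how unequal variances are handled

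*Protocol article*

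**What the plan says.** Section 2.8 (Sample size calculation) bases the size on the one-year rise in quality of life, "specifically the physical component score change of the SF-36 questionnaire V2.0". From an earlier study it takes a "baseline quality of life physical component score of 48.4 + - 5.8 at program initiation and 53.3 + - 3.9 after 12 months", and it adds: "We estimated an increased score to 55 + - 7.0 for CTR patients". The result is stated as "The sample size calculation, using the Hotelling Lawley Trace test, resulted in a sample size of n = 268 per group", with "power = 0.8 and alpha = 0.05". A 10% allowance for loss brings this to 300 per group. The same paragraph expects one telerehabilitation (CTR) patient for every two center-based patients and aims for 300 and 600, so that there are enough to match.

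Section 2.9 (Statistical analysis) says: "Continuous data will be analysed with the independent T-Test (or Mann-Whitney U test for non-normal distribution of data". ANOVA or Kruskal-Wallis covers more than two groups. The only multivariable method is multinomial regression, and that is for programme choice. The section does not say whether the t-test takes the 12-month score or the change from baseline, nor whether variances are pooled.

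On the data available, section 2.7.1 (Questionnaires) says: "Participants evaluate quality of life at baseline, three months and twelve months using the 36-Item Short Form Health Survey (SF-36) version 2.0". The Abstract places the primary endpoint at three and twelve months, and the Introduction says: "We will compare quality of life, physical activity, and modifiable risk factors before, during and after program completion".

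**The concern.** Three things in section 2.9 deserve attention.

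- **Baseline.** The study is sized on change with a multivariate repeated-measures test, and every participant in either programme has a baseline PCS. The named analysis contains no model that uses baseline as a covariate or handles the two follow-up visits together. Precision that costs nothing to collect may go unused.
- **Test chosen by the data.** Letting observed normality decide between a t-test and a rank test means the data decide whether the primary result is a mean difference or a rank comparison.
- **Unequal variances.** The only 12-month SDs in the article are 7.0 for CTR, the smaller group, and 3.9 from the earlier study. If 3.9 describes the larger center-based group, a pooled-variance t-test and a Mann-Whitney test read as a test of location reject too often.

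**Working it through.** **Inputs from section 2.8:** 12-month PCS 55 (SD 7.0) for CTR; 53.3 (SD 3.9) and baseline SD 5.8 from the earlier study; power 0.80; alpha 0.05; 268 per group; 300 and 600 targeted. The difference is 55 − 53.3 = 1.7.

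**Assumptions not in the document:** two-sided alpha; a baseline to 12-month correlation ρ, shown over a range; and, for step 4 and the last line of step 2, SD 3.9 read as the center-based SD.

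**1. The plan's own figure.** n = 2(1.96 + 0.8416)² × 7.0² / 1.7² = 2 × 7.849 × 49 / 2.89 ≈ 266.2, so 267 per group. The exact noncentral-t version gives 268. A two-time Hotelling-Lawley group-by-time test with SD 7.0 at both times and ρ = 0.5 also gives 268. Combining 7.0 with 3.9 gives only 175–176, so 3.9 is not needed to obtain the stated n. For loss: 268 / 0.9 ≈ 298, rounded to 300.

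**2. Power of the unadjusted 12-month comparison.** SE = 7.0 × √(2/268) = 0.605. Power = Φ(1.7/0.605 − 1.96) = Φ(0.85) = 0.80. The target is met. With SDs 7.0 and 3.9 and unpooled variances, power is 0.93 at 268:268 and 0.97 at 300:600.

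**3. What baseline adjustment would add.** This uses 268 per group and SD 7.0 in both groups. ANCOVA multiplies the variance by 1 − ρ², if baseline is balanced between programmes. A change score, with equal SDs at both times, multiplies it by 2(1 − ρ).

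| ρ | ANCOVA factor | ANCOVA power | n per group for 80% (ANCOVA) | Change-score factor | Change-score power |
|---|---|---|---|---|---|
| 0.3 | 0.91 | 0.84 | 243 | 1.40 | 0.66 |
| 0.5 | 0.75 | 0.90 | 200 | 1.00 | 0.80 |
| 0.6 | 0.64 | 0.94 | 171 | 0.80 | 0.88 |

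Power is Φ(1.7 / (0.605 × √factor) − 1.96). The n values use the normal approximation, for which the unadjusted figure is 267. At ρ = 0.5 a change score gains nothing over the raw score.

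**4. Type I error with SDs 7.0 (n = 300) and 3.9 (n = 600), raw 12-month scores.**

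- Pooled variance = (299 × 49 + 599 × 15.21) / 898 = 26.46; pooled SE = √(26.46 × (1/300 + 1/600)) = 0.364.
- True SE = √(49/300 + 15.21/600) = 0.434.
- Ratio = 0.837, so the true error is 2(1 − Φ(1.96 × 0.837)) ≈ 0.101. Simulation with 100,000 runs gives 0.1005.
- Welch's test on the same simulated data: 0.049. Mann-Whitney (3,000 runs): about 0.08.
- Pooled test on change scores, baseline SD 5.8 in both groups, ρ from 0 to 0.8: 0.072 down to 0.064.
- Pooled test at 300:300: 0.050.

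**The case against.** The strongest reply is that section 2.9 may already agree with section 2.8. The sizing paragraph quotes only baseline and 12-month values. With two groups and two times, the Hotelling-Lawley group-by-time test is the pooled independent t-test on change scores. A reader might infer that the sizing test and the analysis test contradict each other, or that baseline is ignored; the text proves neither, because the t-test could be run on change. This stands. It does not remove the efficiency point, since ANCOVA has the smaller variance for any ρ below 1 when baseline is balanced.

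A second reply is that the gains in step 3 rest on a correlation the article does not give and on balanced baseline scores. Patients choose their programme, so imbalance left after matching would shrink the gain. This also stands, and the figures are best read as upper values for each ρ.

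A third is that SD 3.9 is reported as a result of the cited study, never as the assumed center-based SD, and that pooling, raw scores and an analysed 1:2 ratio are all left open. Welch's test is also an independent t-test, and the 600 may serve only as a pool for 1:1 matching. This stands too. Nor would adopting Hotelling-Lawley for the analysis help, because it assumes a common covariance.

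Finally, covariance structure and variance handling often belong in a statistical analysis plan, and none is shown. That covers the detail. But section 2.9 does not defer the choice: it names a test family for continuous outcomes, and that family is the weaker option for the data being collected.

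**Conclusion.** The point holds as a recommendation to improve and clarify the analysis. Section 2.9 names for continuous outcomes only two-sample tests and their multi-group counterparts, with the choice driven by observed normality, although a baseline PCS and two follow-up scores are collected.

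A reader might conclude that the study is underpowered. It is not: 80% is met at 268 per group under the plan's difference and SD 7.0. The loss is forgone precision, roughly 4, 10 or 14 percentage points of power at ρ of 0.3, 0.5 or 0.6, assuming baseline is balanced after matching.

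A reader might also conclude that the plan doubles its type I error. That follows only if variances are pooled, raw 12-month scores are compared, all 300 versus 600 are analysed, and 3.9 is the center-based SD. The documents fix none of these. Otherwise the excess is smaller (about 6–7% for pooled change scores, about 8% for Mann-Whitney) or absent (about 5% with Welch or at 1:1). It is a separate risk from unequal variances, not a consequence of how the study was sized.

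**What to change.** Name one primary PCS analysis: a repeated-measures model adjusted for baseline score, with programme, visit, programme-by-visit interaction, centre and the matching covariates, and with robust standard errors or programme-specific variances. Make the 12-month programme contrast primary and take the 3-month contrast from the same model. Use Welch's version wherever a two-sample t-test remains, and keep Mann-Whitney as a sensitivity analysis, not as an alternative selected by a normality check.

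The cost is revised wording and slightly more analysis work in the software already named (SPSS or R). No new data or participants are needed.
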